**Data collection, follow up;**

Baseline data will include age, gender, BMI; duration of autoimmune thyroid disease and/or differentiated thyroid cancer, History/details of thyroid cancer (stage, FNA findings, final tumor histopathology, presence of lymph node metastasis thyroglobulin levels- baseline and stimulated, preoperative ultrasound findings, extent of surgery); presence of co-morbidities, details of autoimmune thyroid disease (prior anti-thyroid regimen including duration of discontinuation, thyroid function tests (free thyroxine, triiodothyronine, TSH), and thyroid stimulating immunoglobulins ), duration and history of levothyroxine therapy (in cases with thyroid cancer), results of neck and thyroid ultrasound, measured neck circumference prior to application of device, quality of life scores as measured by a questionnaire. Imaging data would be acquired as outlined above.

1. Study duration and number of study visits required of research participants.

**The study duration for an individual participant is 10 days and for the overall study would be 2 years but hopefully will be completed in 6 months depending on the ease of recruitement of patients.**

1. Blinding, including justification for blinding or not blinding the trial, if applicable.

**Since it is a device placed around the neck, it cannot be performed in a blinded way. Also, it is a pilot study done with the device to gather preliminary data**

1. Justification of why participants will not receive routine care or will have current therapy stopped.

**Participants will get their care according to current standards for thyroid cancer as well as Graves disease treatment**

1. Justification for inclusion of a placebo or non-treatment group.

**There is no placebo group.**

1. Definition of treatment failure or participant removal criteria.

**Participant will be removed if he is unable to use the device for the stipulated period of time. The data in those cases might be insufficient.**

1. Description of what happens to participants receiving therapy when study ends or if a participant’s participation in the study ends prematurely.

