**Personalized Treatment Planning for Radioiodine Therapy of Thyroid Disease**

**Protocol Version 1.0, dated December 17, 2017**

1. **Abstract**

The Collar Therapy Indicator (CoTI), a device placed in cloth collar around the neck resembling a turtle neck sweater collar with a connecting wire and recording box (Fig. 1), has been shown in a single small previously published experience to provide data regarding radioiodine exposure that correlates with conventional methods of measuring I-123 and I-131 uptakes after diagnostic dose administration and/or therapy for thyroid disorders . We hypothesize that the device’s continuous measurement capability will permit more accurate estimates of radiation exposure to thyroid tissue than conventionally employed methods assessing fractional uptake at one or a few time points. It may also provide information about the extent of variability in the absorbed radiation dose among patients with thyroid cancer and hyperthyroidism. By providing more complete information about individual patient’s exposures, it will facilitate more accurate estimation of the administered I-131 dose requirements for both control of hyperthyroidism and thyroid remnant ablation while reducing the need for repeated visits to the clinic for dosimetry measurements. The aims of our project include the following: (1) Compare quantitative imaging-derived thyroid time activity curve to that obtained using the CoTI and to determine the extent to which there is variability in radiation dose predicted using conventional methods to that predicted from measurement of the full Time-Activity Curve (TAC); (2) Evaluate the uptake and clearance kinetics across the 5 patients in each category as proof of principle for a potential larger trial to investigate use of this device in optimizing the administered doses of radioactive iodine to achieve therapeutic goals while minimizing risks of comorbidities, such a post-radioiodine hypothyroidism in patients with Graves disease. (3) Evaluate patient experience, convenience, and discomfort in using the CoTI device with a survey instrument.

1. **Objectives** (include all primary and secondary objectives)

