## Primary Objective;

To perform a pilot (exploratory) study using a novel AG Medical Collar Therapy Indicator (CoTI) to evaluate the variability in radioiodine kinetics across patients treated for hyperthyroid Graves disease and postoperative thyroid remnant ablation for thyroid cancer.

- - For Graves disease, after administration of 0.2 mci I-123 and low dose (200 µCi) I-131, to compare conventional 6, 24, 48 and 72-hour fractional thyroidal radioiodine uptakes with single photon emission (with low-dose computed tomography [SPECT/CT] for quantification and attenuation correction) with the activity measured continuously by the COTI device, which is placed in collar around the neck resembling a turtle neck sweater collar with a wire and recording box.
  - For remnant ablation, after therapeutic administration of 30 mCi I-131, to compare conventional 24, 48, 72 hr. and 7-day SPECT (with low dose CT for quantification and attenuation correction performed at 24, 48, 72 hours and 7 days) with the activity continuously measured by the COTI device, as described above.

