## To obtain detailed early-phase thyroid uptake data using a cervical collar device in the Graves disease and thyroid cancer patients as described above.

1. **Background**

Radioiodine treatment for thyroid disorders represented an early example of individualized medicine. Since its introduction 80 years ago, the therapeutic I-131 dosage has usually been tailored to individual patient requirements based on the uptake of a tracer radioiodine dose . Various techniques have been employed to estimate the administered dose of I-131 for optimal therapeutic benefit . Estimated exposure has typically been extrapolated from the results of activity measurements at one or two time points, e.g., at 4 and 24 hours . We now know that treatment of hyperthyroid Graves disease with these methods lead to a 13-25% rate of failure to cure hyperthyroidism and a 46-80% rate of long-term hypothyroidism in cured patients . Similarly, such relatively crude dosimetry doubtless result in significant overtreatment in the case of remnant ablation for differentiated thyroid cancer.For patients with differentiated thyroid cancer requiring remnant ablation, the administered activity has, in most cases, been derived empirically, ranging between 30-100 mci . The high success rates in ablating remnant thyroid tissue implies that many patients are still treated with higher 131-I doses than required, with potential side effects, such as radiation sialadenitis.

1. **Study Procedures**

This will be an unmasked prospective pilot study involving patients with Graves disease (Group I) and differentiated thyroid cancer (Group II). Five patients in each group will have radiation activity measurements using the COTI devise. All persons in the study will receive 131-I treatment based on the current standards of care for dose estimation.

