**No non-FDA drugs will be administered. The CT scans are expected to be without iodinated contrast agents.**

Date: ____________________

Principal Investigator: _________________

Application Number: ___________

1. **Study Statistics**
2. Primary outcome variable.
3. Secondary outcome variables.
4. Statistical plan including sample size justification and interim data analysis.

This is a pilot study involving 10 patients and hence there are no interim data analysis or conflicts regarding sample size. Descriptive data will be outlined for all the participants tabulating the variables as determined. The intrapatient variability as well as accuracy and precision of the device will be obtained individually for Group I and Group II patients. The correlation (non-parametric) Spearman correlation coefficient will be obtained to assess the relationship between the uptake and findings as obtained by the collar device and conventional methods of uptake measurement.

1. Early stopping rules.

Early Stopping Rules Include but not limited to:

1. Severe, unexplained discomfort with the device. (2) Lack of device tolerability or interference with optimal functioning of daily activity (3) Discomfort after stopping anti-thyroid treatments causing rebound hyperthyrodism
2. **Risks**
3. Medical risks, listing all procedures, their major and minor risks and expected frequency. b Steps taken to minimize the risks.

The following risks are anticipated:

• Pressure sensation and possible skin irritation due to compression of skin around the neck. The patients can remove the collar for a few hours every day to avoid this.

• Transient redness around the neck if the collar is placed too tightly.

• For persons with prior thyroid surgery, the device might give cause an unpleasant rubbing sensation, especially if the surgical scar is very fresh.

• Rarely, it could cause patients to experience discomfort with swallowing, but the patients will be given all the necessary information to prevent this. If the participants feels uncomfortable, he/she can remove the device anytime

• The participants will also receive 1-4 low-dose CT scans. The cumulative radiation doses will be very low. Radiation imposed minimal risk at very low doses.

- The participants will undergo a low dose 0.2 mci I-131 dosing that is not associated with thyroid “stunning” and is much less than the 12 mCI (about 60 times 0.2) that they will receive for theraupetic treatment of graves disease

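### Patients who cannot keep the collar on are removed rather than counted, the required wear period is undefined, and permitted off-neck time is not recorded

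*Protocol*

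**What the plan says.** Under Study Procedures, the item on treatment failure and removal reads "Participant will be removed if he is unable to use the device for the stipulated period of time", followed by "The data in those cases might be insufficient". The next item, on participation that ends early, offers only ordinary practice visits according to the patient's condition.

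The Risks section describes how the collar may be worn. On skin pressure and irritation: "The patients can remove the collar for a few hours every day to avoid this". On discomfort generally, the participant is told that "he/she can remove the device anytime".

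Three statements elsewhere depend on wear:

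- The third aim in the Abstract is to "Evaluate patient experience, convenience, and discomfort in using the CoTI device with a survey instrument".
- The Primary Objective compares conventional uptake "with the activity measured continuously by the COTI device", and the first aim in the Abstract needs the complete time-activity curve.
- On numbers: "Five patients in each group will have radiation activity measurements using the COTI devise".

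**The concern.** In a device pilot meant to inform a larger trial, being unable to wear the device is a result. The rule takes the participant out of the study, not only the collar off the neck, and the reason it gives is data sufficiency. Followed as written, those who remain are selected for tolerating the collar. Readings, survey answers and reasons for stopping that are never collected after removal cannot be restored by later analysis.

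The removal rule also cannot be applied as it stands. It turns on a period that is never defined as wear time, while the Risks section permits daily and unlimited removal. A patient who uses the permitted breaks could be judged compliant by one investigator and removable by another.

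Finally, a collar lying off the neck does not measure the thyroid. If those intervals are not marked, they can enter the time-activity curve as if they were thyroid signal. Initial placement is supervised and standardised to neck landmarks, but no check after self-removal is described, so a shift in geometry on reseating may pass unseen.

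**Working it through.** The Protocol states no dropout rate, power or tolerance figure, so there is no figure of its own to reproduce. The group size is from the Protocol. Removal risks, gap lengths, half-lives and uptake rates are assumptions.

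**Which period is stipulated?** The candidates do not agree, and none is stated as wear time:

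- 10 days: an individual's study duration (Study Procedures).
- 7 days: the period tied to the completion payment (Payment and Remuneration).
- Last collar reading: 24 h in Group I(A), 96 h in Group I(B), day 7 in Group II (Scheduled Imaging times).

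**When is discomfort recorded?** Questionnaires are scheduled on Day 0 in Table A, Days 0 and 1 in Table B, and the first day in Table C, which is before the collar is placed on the I-131 dosing day. The last scheduled adverse-event check is Day 0, Day 1 and the I-131 day respectively. Later intolerance would therefore show mainly as failure to keep wearing the collar, which is the event that triggers removal.

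**Losing one patient from a group of 5.** Exact (Clopper-Pearson) limits for x of n are the 2.5% quantile of Beta(x, n-x+1) and the 97.5% quantile of Beta(x+1, n-x).

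- Patient kept: 1/5 = 20%. Lower limit 1 - 0.975^(1/5) = 0.005; upper limit, from Beta(2, 4), 0.716.
- Patient dropped: 0/4 = 0%. Lower limit 0; upper limit 1 - 0.025^(1/4) = 0.602.

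**Chance that a group loses at least one**, 1 - (1-d)^5 for an assumed removal risk d per patient:

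| d | Chance |
|---|---|
| 5% | 23% |
| 10% | 41% |
| 20% | 67% |
| 30% | 83% |

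**Off-neck gaps.** First approximation: 2/24 = 8.3% and 4/24 = 16.7% of the day. For a closer check, take activity A(t) = exp(-ln2·t/Te)·[1 - exp(-ln2·t/k)], where Te is the effective half-life and k the uptake half-time. For I-131, Te = 60 or 120 h, k = 2 to 6 h, over 96 or 168 h. For I-123, Te = 13 h, k = 4 h, over 24 h. The dose is taken at 9 am, with one gap a day starting at 9 am or 9 pm. The area under A(t) is compared with the area when gap counts are set to zero, and with the area when gaps are masked and interpolated linearly.

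| Isotope | Gap per day | Fall if counted as zero | Error if interpolated |
|---|---|---|---|
| I-131 | 2 h | 7.1-8.7% | up to 0.11% |
| I-131 | 3 h | 10.9-13.0% | up to 0.31% |
| I-131 | 4 h | 14.8-17.3% | up to 0.63% |
| I-131 | 6 h | 23.0-25.9% | up to 1.6% |
| I-123 | 2-4 h | 3.1-18.9% | up to 1.8% |
| I-123 | 6 h | 20.3-27.3% | up to 4.9% |

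The gap itself does little harm. What matters is whether it is known to be a gap. The table does not cover a change of geometry on reseating, which interpolation would not correct.

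**The case against.** The removal item answers a form heading about who leaves participation; it does not define an analysis set. It says only that data might be insufficient, and Study Statistics promises descriptive data on every participant. A reader might infer that removed patients' data are discarded, but the Protocol does not say so. This stands: loss from the results is a risk that the wording leaves open, not a stated exclusion.

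The third aim is a survey, not a proportion tolerating the collar, and answers given on the early questionnaire days would survive a later removal. This also stands, so 1/5 against 0/4 is only an illustration. Device intolerance is also listed among the early stopping rules, so it is a recognised event, though nothing says it will be reported as a result.

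A reader might also infer that off-neck time does bias the curve. Nothing in the Protocol says that off-neck counts will be integrated, and masking them is ordinary analysis-plan content. The named analysis is a Spearman correlation, and collar counts are listed at scheduled visits; gaps between visits would not enter a correlation built on those readings. The full-curve aim remains exposed, and no analysis plan can mask intervals that nobody recorded.

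Lastly, a few hours off a day is not the same as being unable to wear the device, because a stipulated period could include breaks. So the two sections are unreconciled rather than flatly contradictory.

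**Conclusion.** The point holds in a limited form. The removal rule selects on the tolerability that the third aim studies, its wear period is undefined, and it is not reconciled with the freedom to take the collar off. An unseen analysis plan cannot repair what was not collected.

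The size of the effect is conditional. One patient is a fifth of a group, and with so few the intervals are wide either way. The 7-17% fall in I-131 time-integrated activity assumes 2-4 h off per day and off-neck counts treated as signal; with gaps recognised and interpolated, the error is about 0.6% or less under the assumed curves. The documents support neither the claim that device failures are excluded nor the claim that the curves will be biased.

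**What to change.** - Define the stipulated period for each group, and reconcile the removal criteria with the Risks section. No clinical wear rule is proposed here.
- Replace removal with a rule that stopping collar use ends collar readings only. Every patient in whom the collar was placed stays in the analysis set, and readings up to the stop are used.
- Report each stop and its reason as a tolerability outcome, and complete the questionnaire and adverse-event check at the stop. Research imaging with no paired collar reading need not continue.
- Log the times the collar goes off and on. Mask those intervals and interpolate when integrating.
- Recheck collar position against the stated landmarks at scheduled visits.

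The cost is revised wording, one log line, a questionnaire and adverse-event check at any early stop, a position check at visits already planned, and small analysis work. No patients, imaging or extra visits are added.

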**The participants will be followed up in our practice for visits as determined by their medical condition.**

1. **Inclusion/Exclusion Criteria**

**Inclusion criteria(adults age 21-65):**

**Group I**

Patients with Graves disease confirmed by laboratory testing and who are likely

candidates for I-131 ablation therapy.

Patients being cared for at the Johns Hopkins Hospital East Baltimore and Bayview Campuses

Patients able to understand English and able to follow instructions.

**Group II**

Patients with intermediate and high risk differentiated thyroid cancer requiring radioiodine remnant ablation or moderately high dose I-131 for treatment of residual cervical disease.

Patients receiving care at the Johns Hopkins Hospital- Main campus as well as Bayview Hospital.

Persons able to understand simple English and able to follow instructions.

**Exclusion Criteria;**

- Patients with diseases involving cervical spine (e.g., spondylosis and severe degenerative joint disease).

-Recent iodinated contrast exposure within 8 weeks of the study

-Persons with contraindications for radioactive iodine therapy (e.g.,pregnant women)

1. **Drugs/ Substances/ Devices**
2. The rationale for choosing the drug and dose or for choosing the device to be used.

Our overall objective is to provide the optimal dose to each patient. This study will apply a novel “wearable” radiation detection technology to determine continuous cervical measurements over days following tracer radioiodine administration will provide information that permits the tailoring of subsequent therapeutic radioiodine doses more precisely to improve clinical outcomes, as described above.The actual therapeutic dose decisions in this pilot trial, however, will not be based on the collar device measurements. Patients with Graves disease will receive 180-200 µCi I-131 per gram of estimated gland mass based on the conventional method of dose calculation, based on a 24-hour % uptake and gland volume. Most patients with thyroid cancer would receive the 30 mCi dose for remnant ablation prior to the placement of the COTI device, as per the American Thyroid Association (ATA) guidelines.

1. Justification and safety information if FDA approved drugs will be administered for non-FDA approved indications or if doses or routes of administration or participant populations are changed.

**No non-FDA drugs will be administered. The CT scans are expected to be without iodinated contrast agents.**

Date: ____________________

Principal Investigator: _________________

Application Number: ___________

1. **Study Statistics**
2. Primary outcome variable.
3. Secondary outcome variables.
4. Statistical plan including sample size justification and interim data analysis.

This is a pilot study involving 10 patients and hence there are no interim data analysis or conflicts regarding sample size. Descriptive data will be outlined for all the participants tabulating the variables as determined. The intrapatient variability as well as accuracy and precision of the device will be obtained individually for Group I and Group II patients. The correlation (non-parametric) Spearman correlation coefficient will be obtained to assess the relationship between the uptake and findings as obtained by the collar device and conventional methods of uptake measurement.

1. Early stopping rules.

Early Stopping Rules Include but not limited to:

1. Severe, unexplained discomfort with the device. (2) Lack of device tolerability or interference with optimal functioning of daily activity (3) Discomfort after stopping anti-thyroid treatments causing rebound hyperthyrodism
2. **Risks**
3. Medical risks, listing all procedures, their major and minor risks and expected frequency. b Steps taken to minimize the risks.

The following risks are anticipated:

• Pressure sensation and possible skin irritation due to compression of skin around the neck. The patients can remove the collar for a few hours every day to avoid this.

• Transient redness around the neck if the collar is placed too tightly.

• For persons with prior thyroid surgery, the device might give cause an unpleasant rubbing sensation, especially if the surgical scar is very fresh.

• Rarely, it could cause patients to experience discomfort with swallowing, but the patients will be given all the necessary information to prevent this. If the participants feels uncomfortable, he/she can remove the device anytime

• The participants will also receive 1-4 low-dose CT scans. The cumulative radiation doses will be very low. Radiation imposed minimal risk at very low doses.

- The participants will undergo a low dose 0.2 mci I-131 dosing that is not associated with thyroid “stunning” and is much less than the 12 mCI (about 60 times 0.2) that they will receive for theraupetic treatment of graves disease

1. Plan for reporting unanticipated problems or study deviations.

If there are unanticipated problems, there will be a documentation as per the IRB rules and incident report guidelines. If there are severe unanticipated problems, the study would be discontinued.

1. Legal risks such as the risks that would be associated with breach of confidentiality.

Legal risks include;

- Breach of confidentiality
- Damage to device and lack of compensation for it
- Risks associated with performing a CT scan

1. Financial risks to the participants.

The medical cost of injury due to unanticipated events during the course of the study

Data and Safety Monitoring Plan:

Routine and continuous monitoring for human subject safety events will be undertaken by the Principal Investigator. In addition, the PI, working with the study staff, will oversee the progress of the study and review participant data for untoward events that are anticipated or unexpected.

Adverse events will be reviewed promptly and assessed for trends or to isolate risks not previously identified. Any serious adverse events will be communicated to the IRB per JHMI IRB policies.

1. **Benefits**
2. Description of the probable benefits for the participant and for society.

This study will apply a novel “wearable” radiation detection technology to determine continuous cervical measurements over days following tracer radioiodine administration will provide information that permits the tailoring of subsequent therapeutic radioiodine doses more precisely to improve clinical outcomes, as described above.

The project aims to explore a promising technology for individualizing therapy by assessing the individual variability in the I-123/I-131-time activity curves, minimizing the risk of 131-I administration while achieving highest possible cure rates by tailoring the I-131 dose and lower the need for frequent follow up visits -laboratory and imaging evaluation and health care costs overall.

1. **Payment and Remuneration**
2. Detail compensation for participants including possible total compensation, proposed bonus, and any proposed reductions or penalties for not completing the protocol.

The participants will be compensated with a gift card of 25 USD per visit that is part of the research. The standard of care visits will not be compensated. At the end of the 7 days period,the participants will receive a 50 USD for compliance and completion.

There are no penalties for completing the protocol except that the gift cards will have to be returned back.

1. **Costs**
2. Detail costs of study procedure(s) or drug (s) or substance(s) to participants and identify who will pay for them.

The study is being funded by a small grant received by the Thyroid Tumor Center (under the stewardship of [name]) that is a subsidiary of the Division of Endocrinology, Department of Medicine, Johns Hopkins Hospital.

|  |  | ***Run-***  ***Up-days***  ***0*** | ***Day 0***  ***9.00 am*** | ***Day 0***  ***3 pm*** | ***Day 1***  ***9 am*** | ***Follow up***  ***Day***  ***7*** |
| --- | --- | --- | --- | --- | --- | --- |
|  |  | ***-4 ± 1*** |  |  |  |  |
| ***Stop anti-thyroid meds*** | | ***X*** |  |  |  |  |
| ***I-123 dose*** | |  | ***X*** |  |  |  |
| ***COTI measurement*** | |  | ***X0*** | ***X0*** | ***X0*** |  |
| ***Uptake Measurement by probe (SOC)*** | |  | ***X*** | ***X*** | ***X*** |  |
| ***I-123 Planar scan*** | |  |  | ***X*** |  |  |
| ***Informed Consent*** | |  | ***X0*** |  |  |  |
| ***Review Eligibility*** | |  | ***X0*** |  |  |  |
| ***Medical History*** | |  | ***X*** |  |  |  |
| ***Physical Exam*** | |  | ***X*** |  |  |  |
| ***Vital Signs*** | |  | ***X*** |  |  |  |
| ***Clinical Labs*** | |  | ***X*** |  |  |  |
| ***Pregnancy Test-eligible*** | |  | ***X*** |  |  |  |
| ***Place Collar*** | |  | ***X0*** |  |  |  |
| ***Give instructions*** | |  | ***X0*** |  |  |  |
| ***Questionnaires*** | |  | ***X0*** |  |  |  |
| ***Adverse Events*** | |  | ***X0*** |  |  |  |
| ***Concomitant***  ***Medications*** | |  | ***X0*** |  |  |  |

***Table A Schedule of Visits after 123 dose for Graves disease Patients – All the visits marked with superscript (o)are part of research-Imaging schedule after I-123 dose***

|  | ***Visit***  ***No.*** | ***Run-***  ***up***  ***0*** | ***Day***  ***0***  ***9 am*** | ***Day***  ***1***  ***9 am*** | ***2***  ***9***  ***am*** | ***3***  ***9***  ***am*** | ***4***  ***9***  ***am*** | ***5*** | ***6*** | ***Follow-***  ***up***  ***7***  ***9am*** |
| --- | --- | --- | --- | --- | --- | --- | --- | --- | --- | --- |
| ***Activity*** | ***Days*** | ***-4 ± 1*** | ***0*** | ***1*** | ***2*** | ***3*** | ***4*** | ***5*** | ***6*** |  |
| ***Stop thionamide***  ***anti-thyroid meds*** | | ***X**** |  |  |  |  |  |  |  |  |
| ***I-131 200 µ administration*** | |  | ***X**** |  |  |  |  |  |  |  |
| ***Uptake Measurement*** | |  | ***X**** | ***X**** |  |  |  |  |  |  |
| ***Informed Consent*** | |  | ***X**** |  |  |  |  |  |  |  |
| ***Review Eligibility*** | |  | ***X**** |  |  |  |  |  |  |  |
| ***Medical History*** | |  | ***X**** |  |  |  |  |  |  |  |
| ***Physical Exam*** | |  | ***X**** |  |  |  |  |  |  |  |
| ***Vital Signs*** | |  | ***X**** |  |  |  |  |  |  |  |
| ***Clinical Labs*** | |  | ***X**** |  |  |  |  |  |  |  |
| ***Pregnancy Test*** | |  | ***X**** |  |  |  |  |  |  |  |
| ***Place Collar*** | |  | ***X**** |  |  |  |  |  |  |  |
| ***Give instructions*** | |  | ***X**** |  |  |  |  |  |  |  |
| ***Questionnaires*** | |  | ***X**** | ***X**** |  |  |  |  |  |  |
| ***SPECT $*** | |  | ***X* 3pm*** | ***X**** | ***X**** | ***X**** |  |  |  |  |
| ***COTI measurement$*** | |  | ***X* 3pm*** | ***X**** | ***X**** | ***X**** | ***X**** |  |  |  |
| ***Low dose CT for attenuation correction*** | |  |  | ***X**** |  |  |  |  |  |  |
| ***Adverse Events*** | |  | ***X**** | ***X**** |  |  |  |  |  |  |
| ***Medications*** | |  | ***X**** | ***X**** |  |  |  |  |  |  |

***Table B- Imaging schedule for Graves disease low dose I-131 scan, COTI measurement and SPECT CT at 3 pm that day-The schedule marked with superscript are part of the research.This is a research scan.***

| ***SCHEDULE OF PROCEDURES*** | | | | | | | | | | | |
| --- | --- | --- | --- | --- | --- | --- | --- | --- | --- | --- | --- |
|  | ***Visit***  ***No.*** | ***Run-***  ***up***  ***0*** | ***Day***  ***1***  ***Time***  ***9.00 am*** | ***2***  ***9***  ***am*** | ***3***  ***9 am*** | ***4***  ***9 am*** | ***5***  ***9***  ***am*** | ***6*** | ***7*** | ***8*** | ***Day***  ***11*** |
| ***Activity*** | ***Days*** | ***-4 ± 1*** | ***0*** | ***1*** | ***2*** | ***3*** | ***4*** | ***5*** | ***6*** | ***7*** |  |
| ***Low iodine diet*** | | ***-14 +/-1 day*** |  |  |  |  |  |  |  |  |  |
| ***Informed Consent*** | |  | ***X*** |  |  |  |  |  |  |  |  |
| ***Review Eligibility*** | |  | ***X1*** |  |  | ***X1*** |  |  |  |  |  |
| ***Medical History*** | |  | ***X1*** |  |  |  |  |  |  |  |  |
| ***Physical Exam*** | |  | ***X1*** |  |  |  |  |  |  |  |  |
| ***Vital Signs*** | |  | ***X1*** |  |  | ***X1*** |  |  |  |  |  |
| ***Clinical Labs*** | |  | ***X1*** |  |  |  |  |  |  |  |  |
| ***Pregnancy Test*** | |  |  | ***X1*** |  |  |  |  |  |  |  |
| ***Thyrogen Injection*** | |  | ***X1*** | ***X1*** |  |  |  |  |  |  |  |
| ***Diagnostic I-123 dose (1 pm)*** | |  |  | ***X1*** |  |  |  |  |  |  |  |
| ***Diagnostic WBS (11 am)*** | |  |  |  | ***X1*** |  |  |  |  |  |  |
| ***I-131 30 mci (1PM)*** | |  |  |  |  | ***X1*** |  |  |  |  |  |
| ***Give instructions*** | |  | ***X1*** |  |  |  |  |  |  |  |  |
| ***Questionnaires*** | |  | ***X1*** |  |  |  |  |  |  |  |  |
| ***COTI placement*** | |  |  |  |  | ***X*** |  |  |  |  |  |
| ***COTI measurement*** | |  |  |  |  | ***X*** | ***X*** | ***X*** | ***X*** | ***X*** | ***X*** |
| ***SPECT*** | |  |  |  |  |  | ***X*** | ***X*** | ***X*** |  | ***X1*** |
| ***Low dose CT for attenuation*** | |  |  |  |  |  | ***X*** |  | ***X*** |  | ***X1*** |
| ***Review of Risks***  ***Benefits*** | |  | ***X*** |  |  |  |  |  |  |  |  |
| ***Adverse Events*** | |  | ***X1*** | ***X1*** |  | ***X1*** |  |  |  |  |  |
| ***Concomitant***  ***Medications*** | |  | ***X1*** | ***X1*** |  | ***X1*** |  |  |  |  |  |

***Table C -Thyroid Cancer Patients-The events not marked with a superscript 1 are part of research. The events in red are part of research protocol. Imaging and visit schedule for thyroid cancer***
